## Abstract

**Introduction:**

There is a significant treatment gap, with only a few community-based services for people with schizophrenia in low-income and middle-income countries. Poor treatment adherence in schizophrenia is associated with poorer health outcomes, suicide attempts and death. We previously reported the effectiveness of supervised treatment in outpatients for schizophrenia (STOPS) for improving treatment adherence in patients with schizophrenia. However, STOPS was evaluated in a tertiary care setting with no primary care involvement, limiting its generalisability to the wider at-risk population. We aim to evaluate the effectiveness of STOPS+ in scaling up the primary care treatment of schizophrenia to a real-world setting.

**Methods and analysis:**

The effectiveness of the STOPS+ intervention in improving the level of functioning and medication adherence in patients with schizophrenia in Pakistan will be evaluated using a cluster randomised controlled trial design. We aim to recruit 526 participants from 24 primary healthcare centres randomly allocated in 1:1 ratio to STOPS+ intervention and enhanced treatment as usual arms. Participants will be followed-up for 12 months postrecruitment. The sample size is estimated for two outcomes (1) the primary clinical outcome is level of functioning, measured using the Global Assessment of Functioning scale and (2) the primary process outcome is adherence to treatment regimen measured using a validated measure. An intention-to-treat approach will be used for the primary analysis.

**Ethics and dissemination:**

Ethical approval has been obtained from Keele University Ethical Review Panel (ref: MH-190017) and Khyber Medical University Ethical Review Board (ref: DIR-KMU-EB/ST/000648). The results of the STOPS+ trial will be reported in peer-reviewed journals and academic conferences and disseminated to local stakeholders and policymakers.

**Trial registration number:**

ISRCTN93243890.

Strengths and limitations of this studyThis study aims to evaluate an approach that can be used for scaling up treatment for schizophrenia in resource poor settings and specifically addresses the gap in schizophrenia treatment.To the best of our knowledge, this is first study that uses a directly observed treatment short-course approach translated from an infectious disorder, that is, tuberculosis to a non-communicable disorder for scaling up the treatment for schizophrenia.The intervention involves primary care in treatment of schizophrenia in community, which is rarely done in low-income and middle-income country.The trial is powered two primary outcomes (1) a clinical outcome measure—Global Assessment of Functioning and (2) a process outcome measure—adherence to medication.The measurement of treatment adherence is based on a subjective measure, that is, reporting from patients and carers that cannot be objectively validated.

## Introduction

Schizophrenia is one of the leading causes of years lived with disability, especially in low-income and middle-income countries (LMICs).^1^ Existing evidence-based interventions for schizophrenia have been poorly implemented and most LMICs have large treatment gap for schizophrenia.^2^ The treatment gap represents the disparity between the true prevalence of a disorder and the treated proportion of individuals diagnosed.^3^ Pakistan has one of the largest treatment gaps for schizophrenia, at an estimated 96%, this is contrast to an estimated median of 32.2% globally and 69% in LMICs.^4 5^ This treatment gap is attributed to a number of factors including poor treatment adherence with average non-treatment adherence rates of about 50% in schizophrenia,^4^ level of disability, a lack of primary care involvement and little to no access to treatment.^5^ This is a particularly important factor in rural areas, where healthcare resources are often diminished in comparison to urban centres.^6^ While the cost of antipsychotic medication in Pakistan is relatively low, economic and logistical factors remain significant barriers to medication access^7^ and the purchase of antipsychotic medication is often at the expense of other forms of essential out-of-pocket healthcare or even food.^8^

Reducing the treatment gap for schizophrenia in LMICs is critical. Medication non-adherence in patients with schizophrenia is associated with 2.8 times increased risk in hospital admission.^9^ The risk of death in patients who receive even minimal treatment is significantly reduced compared with patients receiving no treatment at all.^10^ Furthermore, untreated psychosis can at least double the costs of managing chronic comorbid physical health conditions, leading to an increased stress on an already overburdened healthcare system.^11^

We previously reported a randomised controlled trial (RCT) of supervised treatment in outpatients for schizophrenia (STOPS) in Peshawar, Pakistan.^12^ STOPS was developed using the Medical Research Council framework for complex interventions^13^ and was modelled on the directly observed treatment short-course (DOTS) intervention to improve treatment adherence for people with tuberculosis (TB). The DOTS approach involves a TB worker or a family member directly supervising the patient taking all medication and recording this.^14^ DOTS is one of the most successful public health interventions and has been shown to be as highly effective in the community as it is in specialist clinics, which in addition to its accessibility and low cost, which make it a highly appropriate intervention model for LMICs. Using the similar approach, STOPS intervention involved a family member of a person with schizophrenia observing and recording that medication had been taken. The family member is trained for this purpose. A previous evaluation of STOPS in a tertiary care setting showed that the STOPS significantly improved treatment adherence and functioning as well reducing patient symptoms.^11^

The original STOPS intervention was evaluated in a tertiary care setting by mental health professionals, with no primary care involvement, limiting its scaling up and generalisability. Through a programme of qualitative work with key stakeholders in Pakistan, including patients, carers, healthcare professionals, researchers and local traditional healers, we adapted the STOPS model to STOPS+ with the aim of scaling up the intervention and involving primary care in the management of schizophrenia.

Here, we outline the protocol for evaluating the STOPS+ in a real-world setting using a cluster RCT design.

## Methods and analysis

### Objectives

#### Primary objective

The primary objective is to evaluate the clinical effectiveness of the STOPS+ intervention in improving medication adherence and functioning in patients with schizophrenia compared with enhanced treatment as usual (ETAU) in primary care in Pakistan.

#### Secondary objectives

To evaluate the cost-effectiveness of the STOPS+ intervention compared with ETAU.To assess the effectiveness of STOPS+ in reducing family/caregiver burden and stigma in the community.To evaluate whether STOPS+ leads to physical health improvement in patients with schizophrenia.To investigate the implementation of STOPS+ in a primary care setting and the acceptability of STOPS+ for service users and healthcare providers, assessing the impact of STOPS+ in the wider healthcare system.

### Study setting

The intervention will be implemented and evaluated in the Peshawar district of Khyber Pakhtunkhwa (KP). KP is one of four provinces in Pakistan located in the North West region with an estimated population of 20.7 million. Health expenditure in Pakistan is about 1% of the gross domestic product with no separate provision for mental health services. The primary healthcare (PHC) facilities in KP are provided by a network of basic health units, civil dispensaries and rural health centres. Typically, each PHC facility consists of a primary care physician, a multipurpose PHC technician (MT) and a female health worker.^15^ Training PHC providers to manage mental health conditions and the incorporation of mental health services into primary care are both envisaged in the current health policy but have not yet been fully realised.^5^

### Trial design

A cluster RCT will be used to investigate the efficacy of the STOPS+ intervention compared with ETAU in people living with schizophrenia. The cluster RCT design will help to evaluate the implementation of STOPS+ at the healthcare facility level and to minimise the contamination of intervention and control arms.

### The control: ETAU

Typically, in Pakistan, treatment for schizophrenia consists of accessing hospital-based psychiatric services with little to no involvement of PHC and a limited provision of medication from the hospital pharmacy. ETAU provided in the control clusters will include the treatment received by patients’ routine healthcare setting, which includes treatment provided by a psychiatrist in the outpatient clinics of the psychiatry department of the local hospital and brief counselling about the treatment and outcome of the disorder. Patients may be admitted to an inpatient unit at the hospital. This will be enhanced in the control cluster PHCs with training provided to PHC physicians in WHO Mental Health Gap Action Programme (MhGAP) (https://www.who.int/mental_health/mhgap/en/t) in addition to the regular and reliable provision of psychotropic drugs at the PHC. The patients will be informed that the antipsychotic medication is available in the PHC centre and they can access the centre for supply of medication. The PHC physician will have the option to liaise with the treating psychiatrist, as provided in the MhGAP guidelines.

### STOPS+ intervention

The STOPS+ intervention will consist of the ETAU plus the following components.

#### Supervision by a trained family member for dispensing and administering medication

A family member who is living with the patient for a minimum of 6 months prior to recruitment to the trial will be nominated by the patient. The family member will dispense medication, observe that is has been taken correctly and record this information on a simple sheet of paper designed and used in the previous STOPS trial.^9^ Family members will be reminded to administer the medication by an automated text message system, which will also request a response once the medication has been taken correctly. The text message reminders will be sent everyday for the first 3 months after starting the treatment. If the family member does not have access to a mobile phone, a handset and training in using it will be provided.

A multipurpose technician (MPT) from each PHC centre will provide training to family members for the storage and administration of the medication, recording when the medication has been taken correctly and the importance of maintaining the family dynamic.

#### Treatment for schizophrenia at PHC level supervised by mental health professionals

Ongoing management and monitoring of the patient’s schizophrenia will take place at their PHC centre by the PHC physician, under the supervision of the treating psychiatrist with the help of the mobile technology platform smartphone for monitoring, assessment and remote treatment (SMART). SMART will provide two-way communication between mental healthcare professionals. One month’s supply of medication will be made available, via their PHC, to the family member. The automated messaging system will also remind the family member about collecting the following month’s supply.

#### Monitoring the availability of essential psychotropic medication and their side effects

A kit to monitor the supply of medication will be used to monitor the availability and supply of psychotropic medication. This will consist of (a) a cupboard dedicated specifically for the storage of psychotropic medication, (b) a tracking sheet used to monitor the stock levels and (c) a simple checklist for monitoring side effects of antipsychotics.

### Assessment of barriers and facilitators of implementation of the intervention

The use of theory to inform the development of behaviour change interventions is strongly advocated by experts in the field. We have designed the process of implementation using theory developed for implementation and tested previously in UK Primary Care Practice.^16 17^ We will evaluate the barriers and facilitators to implementation of the intervention using qualitative methods. We will hold at least four focus groups (with patients and carers, MPTs, traditional and faith healers and primary care clinicians) in which we will explore the barrier and facilitators to supervising the treatment of schizophrenia in the community, modification of the STOPS programme to STOPS+ for use in the community and the present status of schizophrenia care in the community

### Patient and public involvement

STOPS+ is underpinned by culturally appropriate and context-bespoke patient and public community engagement and involvement at every stage of the project (intervention development, RCT and process evaluation). The STOPS+ intervention will be refined with input from the key stakeholder groups including patients, carers, health professionals, local councillors, community leaders such as religious leaders and community experts and policymakers. Small group meetings using local Jirgas (Jirga is traditional, local participatory and decision-making body which is well established in Pathan culture and brings together local tribal, ethnic and religious leaders) will help in community engagement.

### Primary outcome measure

In view of the pragmatic nature of the trial, we will use two distinct primary outcomes:

The primary clinical outcome will be the level of functioning, measured using the Global Assessment of Functioning (GAF) scale.^18^ GAF is a commonly used tool in schizophrenia, particularly for the pragmatic trials.^19^The primary process outcome will be adherence to treatment regimen. The adherence to treatment will be measured using a questionnaire adapted from Herz *et al*.^20^ This measure for assessing treatment adherence was successfully used in our previous STOPS study.^9^

### Secondary outcomes

The details of secondary outcomes and the standardised instruments for measuring these are given in table 1. These instruments will measure secondary outcomes such as physical health outcomes, family/caregivers burden and internalised stigma.

**Table 1 T1:** Description of outcome measures and instruments

Domains measured	Measure
Sociodemographics	Age
	Gender
	Years in education
	Marital status
	Work status
	Mini-Neuropsychiatric Interview for diagnosis of schizophrenia^21^
Physical health	Body mass index
	Blood pressure
	Waist circumference
Primary outcomes	
Level of functioning	Global Assessment of Functioning^18^
Level of adherence	Treatment adherence rating scale^20^
Secondary outcomes	
Mental state and psychiatric symptoms	Brief Psychiatric Rating Scale^40^
Caregivers’ burden	Family Burden Scale^41^
Perceived stigma	Internalised Stigma of Mental Illness^42^
Side effects of antipsychotic medication	Glasgow Antipsychotic Side-Effects Scale^43^
Cost of care	Client Service Receipt Inventory^44^
Quality of life and cost-effectiveness	EuroQol (EQ5D)^45^
Illness severity, improvement and response to treatment	Clinical Global Impression Scale^46^
Drug use	DAST Drug Screening Tool^47^
Depression	Patient Health Questionnaire^48^
Suicide Ideation	Suicide Behaviours Questionnaire Revised^49^

DAST, Drug Abuse Screening Test; EQ5D, EuroQol 5 Dimension.

### Eligibility criteria

Patients will be eligible for inclusion if they

Have a diagnosis of schizophrenia (F20.9) or schizoaffective disorder (F25.9) based on the International Classification of Disease 10 criteria assessed using the Mini-International Neuropsychiatric Interview.^21^Are aged between 17 and 65 years.Do not meet the criteria for remission as defined by the Remission in Schizophrenia Working Group.^22^Have capacity and are able to give informed consent.Have a family member who is also willing to participate in the trial and supervise the treatment after training by the research team.

Exclusion criteria will be kept to a minimum to ensure that the study can examine the real-world implementation of the STOPS+. The patients who can not participate in the study due to one of following reasons will be excluded (1) a serious or unstable medical illness, (2) evidence of learning disability, (3) severe drug dependence requiring treatment and/or detoxification and (4) pregnant or breast-feeding.

### Duration of treatment and follow-up

Both groups will be followed up for 12 months after recruitment in the study. The follow-up using face-to-face assessments will be carried out by trained research assistants in a health facility which is not part of participating PHCs to preserve the blindness of clusters. All of the outcomes will be measured at baseline, at 6 months and at 12 months by research assistants.

### Participant identification

Participants will be identified from two possible sources (1) patients living in the area of the participating PHCs and presenting at psychiatry outpatient services of the hospitals in the area and (2) potentially eligible patients identified by the PHC workers during community engagement or attending the PHCs. Eligible participants will be informed about the trial orally by the PHC staff and written information will be provided in the local language (Urdu). Those interested in taking part will be asked to give written informed consent. For participants who cannot read and write, witnessed oral consent and a thumbprint in lieu of a signature will be used. The witness will not be a member of the research team. The procedure has been used in our previous trials in the area.^23^

### Randomisation and allocation concealment

Randomisation will occur at the PHC level, where PHCs will be allocated at a ratio of 1:1 to either deliver the STOPS+ intervention or ETAU. Twenty-four PHCs will be recruited to the study, 12 will be randomised to deliver ETAU and 12 will be randomised to deliver the STOPS+ programme. PHC randomisation will be stratified by urban/rural setting. Randomisation will be carried out by an independent statistician at the Khyber Medical University (KMU), Peshawar by using a remote computer-generated random sequence. Randomisation and will be based on the list of primary care centres in Peshawar, provided by the health department of KP. The urban/rural classification is determined as per the Peshawar district council. It is not possible to blind study participants from their treatment arm allocation. However, the assessment team that conducts the baseline and follow-up assessments (6 and 12 months) will be masked to the treatment arm of the cluster. The outcome measures will be administered by trained research assessment teams (outcome assessors), who are independent of the intervention team and the team involved in consenting and screening. The outcome assessment will not be carried out at any participating PHC. The assessment teams will be told that they are evaluating two interventions and that there is genuine equipoise about which one is better. Study participants will be instructed to not discuss the PHC they are attending or the treatment details. During all assessments, the primary outcome measures (treatment adherence scale and GAF) will be completed first to minimise the risk of bias in the event of unmasking and, if it occurs, the point of unmasking will be recorded. Sensitivity analyses will be carried out to assess the effect of unmasking on the primary outcomes. The data linking each PHC with treatment allocation status is kept separate from the outcome dataset until the time of the final analysis. The trial statistician will be blind to allocation status.

### Screening, data collection and follow-up

After identification of potentially eligible patients, they will first be orally informed about the trial by one of the health workers in the local Pushto language (MT in the community or a health professional in one of the health facilities mentioned above). They will be asked whether they agree that a member of the research team will provide them with further information about the research. If permission is given, a research assistant will meet with the patient and will request informed consent. The informed consent for participation in the study will be taken within 1 week of the first contact. Participants will be free to decline to participate or withdraw at any time without their routine healthcare being affected. Before taking part in any interviews, oral and written information about the study and its purpose will be provided to respondents in the local language.

After obtaining informed consent, the research assistant will decide whether the patient meets the inclusion criteria and have a family member who is willing to supervise the treatment as specified in the STOPS+ procedures. If the patient is not eligible from the screening assessment, the reason for ineligibility will be explained to the patient and they will be signposted for further advice and to continue to receive treatment at their routine health facility. Eligible patients will be provided with a further participant information sheet about the trial. Additionally, for those in the intervention arm, the nominated relative will receive a participant information sheet about the trial and about the tasks required in supervising the treatment If nominated family member is available with the patient, this information will be provided at the same time. If the family member is not available, patients and the family member will be asked to visit the health facility again within 1 week. The patient and the relative will each be given the opportunity to ask any questions about the trial. The information sheets are provided in Urdu. For illiterate patients, the research assistants will explain the same information in local Pushto language or in Urdu. Following the informed consent, the baseline data will be collected.

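### Only STOPS+ relatives receive the written supervision tasks before baseline, so allocation is open before enrolment is complete and the arms may lose different families

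*Protocol article*

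**What the plan says.** All references are to the Protocol article.

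- **Unit of randomisation** (Randomisation and allocation concealment): "Randomisation will occur at the PHC level, where PHCs will be allocated at a ratio of 1:1". The draw "will be based on the list of primary care centres in Peshawar, provided by the health department of KP", so it needs no patient to have been recruited. The article does not say when it takes place relative to recruitment.
- **Who finds patients** (Participant identification): there are two sources. One is hospital psychiatry outpatients living in the PHC area. The other is "potentially eligible patients identified by the PHC workers during community engagement or attending the PHCs". PHC staff give the first oral information. The following section also allows a health professional at one of the health facilities to do so.
- **Criterion on the relative** (Eligibility criteria), for both arms: "Have a family member who is also willing to participate in the trial and supervise the treatment after training by the research team".
- **Order of entry** (Screening, data collection and follow-up): the patient consents. A research assistant then decides eligibility, including whether a relative will supervise in the way the STOPS+ procedures require. Eligible patients receive a further sheet. In addition, "for those in the intervention arm, the nominated relative will receive a participant information sheet about the trial and about the tasks required". A relative who is not present is asked to come back within a week. Finally, "Following the informed consent, the baseline data will be collected".
- **Masking** (Randomisation and allocation concealment): "It is not possible to blind study participants from their treatment arm allocation". The baseline and follow-up assessors are masked, and so is the trial statistician. The assessors are people "who are independent of the intervention team and the team involved in consenting and screening". Nothing is said about masking that second team.
- **Adjustment** (Statistical analysis): age, gender, baseline GAF, baseline value of the outcome, PHC size and rural/urban setting. No covariate concerns the relative.

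**The concern.** In a cluster trial, randomisation balances the centres. It protects the comparison of patients only if entry does not depend on the arm. Here an arm-specific step lies inside the entry sequence, ahead of baseline. A STOPS+ relative reads what daily supervision involves and can still decline before the patient is counted. An ETAU relative reaches baseline without that sheet and will not be asked to supervise.

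PHC staff also supply some of the patients and make first contact. They deliver the arm-specific care, so they can hardly be unaware of their own centre's arm.

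Family support is likely to bear on adherence, which is one primary outcome, and through it on functioning, which is the other. Masked assessors protect the measurement but not the choice of who is measured. Intention-to-treat analysis starts only after that choice has been made.

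**Working it through.** **Step 1. Where the arms diverge.**

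| Step before baseline | STOPS+ | ETAU |
|---|---|---|
| Identification by PHC workers or hospital clinic | yes | yes |
| Patient consent | yes | yes |
| Willingness of relative judged against the STOPS+ procedures | yes | yes |
| Further sheet for the eligible patient | yes | yes |
| Sheet for the relative on trial and tasks | yes | not stated |
| Return visit within a week if relative absent | yes | apparently not |
| Baseline | yes | yes |

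The written criterion is common to both arms. The divergence comes after the eligibility decision and before baseline. The sheet can be handed out only by someone who knows the allocation, so allocation is open by then. The return visit follows directly on the intervention-arm sheet and refers back to it, which is why it reads as a STOPS+ step; the text does not say so outright.

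**Step 2. Reproduce the plan's precision.** Inputs from Sample size calculation: SD 15, baseline–outcome correlation 0.5, repeated-measures correlation 0.7, loss 20%, ICC 0.01, coefficient of variation of cluster size 0.65, 263 per arm, 24 PHCs.

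- SD of the adjusted two-visit average: 15 × √((1 + 0.7)/2 − 0.5²) = 15 × √0.60 = 11.62.
- Mean cluster size: 526/24 = 21.9, or 17.5 after 20% loss.
- Design effect: 1 + ((0.65² + 1) × m − 1) × 0.01 = 1.302 (m = 21.9) or 1.239 (m = 17.5).
- Effective number per arm: 263 × 0.8 / design effect = 161.6 or 169.8.
- Power for a difference of 4: 87.2% or 88.7% (stated 85–90%). For 6: 99.6% or 99.7% (stated over 90%).

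The stated GAF power is confirmed and is not in dispute. The standard error of the GAF contrast is 11.62 × √(2/169.8) = 1.26.

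**Step 3. Size of a possible GAF shift.** The article gives no refusal rate and no outcome gap, so both are assumptions. If a share p of families is lost in STOPS+ only, and their patients would end d points below those kept, the arms differ by p × d with no treatment effect.

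| p | d = 5 | d = 10 |
|---|---|---|
| 5% | 0.25 | 0.5 |
| 10% | 0.5 | 1.0 |
| 20% | 1.0 | 2.0 |

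**Step 4. Allow for baseline adjustment.** Suppose the gap is equally present at baseline and the SDs are equal. The slope on baseline GAF is then 0.5, and adjustment removes half: 0.25–2.0 becomes about 0.13–1.0 points. A gap that only emerges later, for example through adherence, would be removed less.

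**Step 5. Effect on the test.** For a residual shift b, the two-sided type I error is Φ(b/1.26 − 1.96) + Φ(−b/1.26 − 1.96).

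| Residual b | Type I error |
|---|---|
| 0.13 | 5.1% |
| 0.25 | 5.5% |
| 1.0 | about 12% |
| 2.0 | about 35% |

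**Step 6. Adherence.** With the same p and an assumed gap of 20–40 percentage points, the unadjusted shift is 0.05 × 20 = 1 point to 0.20 × 40 = 8 points. The planned difference is 20 points.

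**The case against.** **A reader might infer that the willingness criterion itself is applied differently in the two arms.** The article does not support this. Willingness is judged before the arm-specific sheet appears, against one standard tied to the STOPS+ procedures, so ETAU relatives may also hear something of the tasks. What is exclusive to STOPS+ is the written sheet and whatever follows from it. The article also does not say that a patient already consented and eligible is removed if the relative then declines; it leaves this open.

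**A reader might infer that consent and screening are carried out with the arm known.** That is an inference. The article states neither when randomisation occurs nor what the research assistant knows before the sheet is given. A condensed article may leave masking of recruiters to the full protocol. What stands is that allocation is open before baseline, and that the masking described does not extend to the recruiting team.

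**A reader might infer that both outcomes are pushed towards STOPS+.** This is plausible but not shown. Families of sicker or less adherent patients could be the keener ones to supervise. Hospital outpatients form one of the two sources, so not every patient is found by PHC staff, and the effect of arm-aware identification has no known sign.

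**The size rests on assumptions.** Neither the refusal range nor the outcome gap comes from the article, and the upper figure of 2.0 points ignores the planned adjustment for baseline GAF. At the low end the effect is negligible.

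These points narrow the mechanism and temper the size. They do not remove the arm-specific step before baseline.

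**Conclusion.** The concern holds in a limited form. Followed as written, the entry sequence opens allocation before enrolment is complete and gives STOPS+ families an extra opportunity to leave before baseline. PHC staff who deliver the allocated care also identify some of the patients. Neither the stated masking nor the covariates address who is admitted.

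This is a risk of recruitment bias in both primary outcomes, not a demonstrated bias. Under the assumed 5–20% differential loss and 5–10 point gap, the GAF shift is 0.25–2.0 points unadjusted and about half that if baseline GAF carries the gap, against a minimum important difference of 4. For adherence the assumed range is 1–8 percentage points against 20. The direction probably favours STOPS+, but the article does not establish it. No power figure is affected.

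The plan should be changed on this point. Confidence is moderate, because the recruiters' knowledge of the arm and the handling of late refusals are inferred or unstated.

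**What to change.** Revise Screening, data collection and follow-up as follows.

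1. Give relatives in both arms the same information sheet at screening, including what supervision would involve, and put the same scripted willingness question to all of them. Apply the same return-visit rule in both arms.
2. Complete eligibility, consent and the masked baseline before any STOPS+-specific sheet or training is released.
3. Keep in the intention-to-treat set any patient whose relative declines after baseline.
4. Where existing staffing allows, keep the assistants who screen and take consent unaware of the PHC's arm, and state this beside the masking of the assessors.
5. Report numbers identified, eligible, refused and enrolled by arm and by identification source. Recruitment began on 1 November 2019 (Ethics and dissemination), so include patients already enrolled; re-ordering can help only those who enter later.

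The cost is an ethics amendment for the shared sheet and the new order of steps. Items 1 to 3 need no extra patients or staff; item 4 is conditional because masking recruiters may affect staffing. A few STOPS+ relatives may decline after baseline instead of before it, which slightly dilutes the estimated effect.
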